## Abstract

Introduction: This study aims to assess the efficacy of the modified kangaroo care lateral position on the thermal stability of preterm neonates versus conventional kangaroo care prone position. Material and methods: A non-inferiority randomized parallel clinical trial. Kangaroo care will be performed in a lateral position for the experimental group and in a prone position for the control group preterm. The study will take place at the neonatal intensive care unit (NICU) of a University Hospital. The participants will be extremely premature infants (under 28 weeks of gestational age) along the first five days of life, hemodynamically stable, with mother or father willing to do kangaroo care and give their written consent to participate in the study. The sample size calculated was 35 participants in each group. When the premature infant is hemodynamically stable and one of the parents stays in the NICU, the patient will be randomized into two groups: an experimental group or a control group. The primary outcome is premature infant axillary temperature. Neonatal pain level and intraventricular hemorrhage are secondary outcomes. Discussion: There is no scientific evidence on modified kangaroo care lateral position. Furthermore, there is little evidence of increased intraventricular hemorrhage association with the lateral head position necessary in conventional or prone kangaroo care in extremely premature newborns. Kangaroo care is a priority intervention in neonatal units increasing the time of use more and more, making postural changes necessary to optimize comfort and minimize risks with kangaroo care lateral position as an alternative to conventional prone position kangaroo care. Meanwhile, it is essential to ensure that the conventional kangaroo care prone position, which requires the head to lay sideways, is a safe position in terms of preventing intraventricular hemorrhage in the first five days of life of children under 28 weeks of gestational age. Trial registration at clinicaltrials.gov: NCT03990116.

## 1. Introduction

Kangaroo care (KC) is a safe and low-cost intervention with an impact on the prevention of many potential complications in neonates and premature infants such as sepsis, brain injury, or mortality [1]. Conventional KC consists of placing the baby vertically between the mother’s breasts or on the father’s thorax, skin-to-skin with their limbs flexed, and in the prone position with the head 90 degrees to the side and slightly extended to ensure proper opening of the airway and to favor visual contact between the mother/father and child [2].

Plentiful evidence is available on the benefits of prone kangaroo care, or skin-to-skin, such as lower mortality (RR 0.64; 95% [CI] 0.46, 0.89), reduced risk of neonatal sepsis (RR 0.53, 95% CI 0.34, 0.83), of hypothermia (RR 0.22; 95% CI 0.12, 0.41), of hypoglycemia (RR 0.12; 95% CI 0.05, 0.32), and of hospital readmissions (RR 0.42; 95% CI 0.23, 0.76) as well as greater hemodynamic stability (lower respiratory rate, greater peripheral oxygen saturation). KC increases the likelihood of exclusive breastfeeding (RR 1.50; 95% CI 1.26, 1.78), and neonates experience less pain, better sleep organization, and more attachment, with better cognitive development and emotional regulation in the first year of life [3,4,5,6,7].

Two of the main complications in premature infants are hypothermia due to increasing heat loss and germinal matrix intraventricular hemorrhage (IVH).

Hypothermia is a major complication observed in extreme prematures due to thermoregulatory center’s physiological immaturity. They also have a greater relationship between the body surface and total body mass, vasomotor control immaturity and limited subcutaneous fat. The skin is also porous, not covered by lanugo or vernix caseosa, and has a thin corneal stratum. Prematures are poikilotherm, having a body temperature that varies according to the outside temperature, so they need greater environmental control, including the temperature and the humidity [8].

Temperature is an outcome that increases the risk of morbidity and mortality in this population. Mohamed et al. [9] found the hypothermia is associated with mortality (OR = 1.89; 1.72–2.09), intra-ventricular hemorrhage (OR = 1.86; 1.09–3.14), bronchopulmonary dysplasia (OR = 1.28; 1.16–1.40) or neonatal sepsis (OR = 1.47; 1.09–2.49), and retinopathy of prematurity (OR = 1.45; 1.28–1.72). Similar results were found in other studies [10]. Laptook et al. [11] found in an adjusted analysis that with each 1 °C decrease in body temperature, sepsis and mortality risks increase by 11 and 28%, respectively.

The ILCOR (International Liaison Committee on Resuscitation) [12] has insisted on the importance of maintaining normothermia (36.5–37.5 °C), especially in more premature infants given that, even though it is rarely the primary cause of death, it is related to increased morbidity and mortality rates and impact of complications such as IVH, bronchopulmonary dysplasia, retinopathy of prematurity, and increased rate of neonatal sepsis or necrotizing enterocolitis [13]. Recommendations to keep up normothermia are high humidity concentrations in incubators (above 80%), use of polyethylene bags or thermal mattresses, and skin-to-skin care [14,15]). Abundant literature is available on hypothermia in premature infants and the effectiveness of KC to prevent it; however, few studies have been carried out in the most vulnerable neonatal population, extremely premature infants [16,17].

However, the greater risk of hypothermia is taking place during neonatal transfer, which is defined as the movement from incubator to kangaroo position on father or mother chest. The reason why this happens is that neonates get in contact with an environment not as controlled as the incubator ones in terms of temperature and humidity. Furthermore, during kangaroo care, parents provide heat to their premature child but not humidity, another reason why the risk of hypothermia increase [18].

Meanwhile, the rate of IVH stands at around 20–38% in children under 28 weeks of gestational age (GA) and is more frequent in the first 72 h of life [19,20]. Thus, the risk of bleeding is inversely related to gestational age and can be attributed to three factors: vascular immaturity of the germinal matrix, deficient extravascular matrix, and cerebral blood flow alterations. In conventional kangaroo care prone position to a premature infant, the head is turned 90 degrees, compressing the internal jugular vein and therefore compromising venous blood drainage. This potential venous congestion leads to increased intracranial pressure, reduced brain oxygenation, and ultimately of the germinal matrix, thus increasing the risk of IVH [21]

KC is a neuroprotective intervention that can improve survival in premature infants [14], becoming the star program at neonatal units around the world; this is the reason to recommend it as soon as it is possible, and for as long time, requiring postural changes of the neonate towards the KC lateral position if KC is prolonged [22,23].

Although some studies have proposed that premature infants with lateral head position have poorer cerebral vascular flow, cerebral oximetry, and greater risk of IVH, evidence of this is scarce and low quality [24]. Thus, recommendations in clinical practice are variable; on occasions, preterms under 28 weeks of GA should be positioned with the head in the midline position for at least the first 72 h and up to the first seven days of life, and with the incubator inclined 15–30 degrees [24,25,26]. This would entail placing extremely premature in the modified KC lateral position during the first 7 days of life, lying on the bare thorax or chest of the mother or father, with the limbs flexed towards the midline and the head neutral and in line with the rest of the body. However, there is no evidence of the effectiveness of modified KC lateral position in relation to thermal. One side lying position could be a thermoregulation challenge, compared with prone position, because there is less skin surface in contact with the skin of the kangaroo provider.

There is no evidence either on hemodynamic stability and the consequences on pain or stress during one side lying position KC.

Meanwhile, clinical practice is also variable in terms of recommending the conventional KC prone position in neonates with an umbilical catheter as it cannot be visually controlled and therefore possible related complications monitored (displacement, bleeding, leakage), with no scientific evidence confirming a greater risk of these adverse events. However, these restrictive clinical practices are found in published studies [27].

## 2. Material and Methods

### 2.1. Aim

The main aim of this study is to assess the efficacy of the modified kangaroo care lateral position on the thermal stability of preterm infants versus conventional kangaroo care prone position. Secondary proposed aims are (a) to compare the number of intraventricular hemorrhage events in relation to the assigned group, prone or lateral position; and (b) to assess the effectiveness of kangaroo care lateral position in alleviating pain versus conventional prone kangaroo care.

### 2.2. Design

The study is designed as a non-inferiority randomized parallel clinical trial.

The CONSORT guidelines for randomized controlled trials will be used. This protocol also adheres to the SPIRIT guidelines (Supplementary Materials: checklist SPIRIT).

### 2.3. Study Setting

The study will be conducted at the NICU of a University Hospital in Madrid, Spain. This NICU is a level-IIIC and a 24/7 open doors for parents. The NICU has 19 beds, with 9 single-family rooms (two rooms are twins) and 8 beds in an open bay and family-centered and developmentally supportive care are implemented in it. Parents are invited to participate and be part of their childcare, as is indicated by the evidence [28]. From the admission, parents work together with staff. The NICU has implemented a standardized parental training program called “Cuidame” (“take care of me”) which teaches parents how to participate gradually.

On the other hand, when preterm birth is expected, parents are informed about different treatment options by the neonatal team. This information includes how important it is to stay next to babies’ incubators, be part of their childcare, and provide early kangaroo care as soon as baby condition permits it. If it is possible, parents can also visit the unit before being admitted.

### 2.4. Study Population

The participants of the study will be all patients admitted to the NICU premature under 28 weeks of GA hemodynamic stability, with a parent (mother or father) who wants to do KC and give their written consent to participate in the study.

The exclusion criteria will be premature infant (a) receiving high-frequency ventilation; (b) in the immediate recovery period from major surgery; (c) with abdominal wall defect; (d) who needs restraints; (e) with hemodynamically unstable; or (f) mother/father with physically or psychologically incapacitating illness.

Nowadays, there is no scientific consensus about the definition “hemodynamically unstable”. For that reason, the research team chose to define it as repeated apneas followed by bradycardia (HR < 100 bpm) as a current participant condition or during handling if it requires an increase in oxygen demands or stimulation for restoring breathing.

Removal criteria: hypothermia or kangaroo care duration under 60 min.

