Premature infants’ axillary temperature will be assessed during kangaroo care. In the event of axillary temperature <36.5 °C, checks will be conducted to ensure the temperature sensor is placed correctly, adding a towel or blanket to the polyethylene bags covering it. The temperature will be reassessed after 15 min, adding another towel or blanket if it remains <36.5 °C. It will be assessed for the third time after 15 min, and kangaroo care will be suspended if the temperature remains <36.5 °C.

If during this time the neonate should have an axillary temperature >37.5 °C, the cover material (towel or blanket) will be gradually removed.

KC sessions can be at any time of the day, with the frequency and duration required by the mother/father, based on a minimum of 60 min. All KC sessions during the first five days of life will be monitored, recording data in the medical record, which will later be extracted and systematized in the study data collection notebook for analysis.

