### 2.10. Outcomes

Primary outcome:
Premature infant axillary temperature.

Secondary outcomes:
Neonatal pain level.Intraventricular hemorrhage number of events.

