### 2.13. Statistical Analysis

Normality associated with each quantitative variable will be analyzed using the test Kolmogorov–Smirnov test.

A descriptive analysis will be performed of the demographic and clinical characteristics of subjects in both treatment groups: quantitative variables will be described by mean or median and their dispersion measurements, standard deviation or interquartile range, respective, as appropriate. Qualitative variables will be described by absolute frequencies and percentages. The descriptive analysis will be accompanied by the 95% confidence interval.

Prior to testing hypotheses, we will check whether both groups are homogeneous in terms of the baseline characteristics, using Student’s *t*-test or Mann–Whitney U for quantitative variables or ANOVA or Kruskal–Wallis if the variable does not follow normal distribution, and if statistically significant differences are found, we will continue with post hoc Bonferroni contrasts or weighted comparisons with Mann–Whitney U. Chi-squared will be used for qualitative variables.

If the groups are heterogeneous, confounding factors will be defined to adapt the final analysis to the main variable.

The effectiveness of KC modified lateral position compared to the KC conventional prone position will be assessed, calculating axillary temperature variation (Student’s t-test or Mann–Whitney U), level of pain (Student’s *t*-test or Mann–Whitney U), and IVH development (Chi-squared) in both groups.

Intention to treat (NNT) and protocol analyses will be performed. Should the results be conflicting, protocol deviations and/or breaches will be analyzed.

Safety analysis in relation to adverse events will be calculated using Pearson’s Chi-squared test or Fisher’s exact test as appropriate.

An explanatory model with stepwise linear regression will be created based on a significance level of 0.1, and confounding variables and their level of importance will be determined.

The statistical significance level will be *p* < 0.05. Data will be analyzed with the Statistical Package for the Social Sciences-IBM SPSS^®^ program version 25.0 (IBM, Chicago, IL, USA).

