### 2.15. Monitoring

An interim analysis is performed on the primary endpoint when 20% of patients have been randomized. The idea is to be able to identify an increase in HIV incidence in the control group, such as other potential hazard events in all participants. In that case, the study would come to a halt. The main investigator will have unblinded access to data and will discuss the results of the interim analysis with the research team.

The trial will not be stopped in case of futility related to the outcome variables because kangaroo care is the current intervention in the neonatal units due to clinically proven benefits, so futility is not sustainable.

The main investigator has the ultimate authority to stop or modify the trial and to ensure the protocol’s continued. He will follow up with all participants, and he will check all kangaroo care sessions are completed as it is referred to in the protocol. If that is not the case, the session will be discarded.

Changes on the protocol will be notified to all team members immediately and keeping all documentation standardized. All updated versions will be available in a digital form, and team members will be noticed during practical and theoretical lectures.

Safety and complications were monitored by identifying kangaroo potential adverse events noted down in the Data Collection Logbook (DCL), such as hypothermia, continuous hemodynamic instability during kangaroo care, or accidental displacement of any therapeutic device. Those events will be collected and analyzed in the first 24 h by the investigator in charge of the session, notifying the main investigator. The main investigator will record this adverse event on the study database, taking the actions required according to the severity and impact.

A committee in charge of data monitoring has not been created, the tracking is carried out by the research team. Non-audits have been scheduled.

Preliminary analyses every 20 new participants will be done to discard a rising HIV incidence in the control group, which would mean the study would come to a standstill.

Established withdrawal criteria are hypothermia or a Kangaroo care session less than 60 min.

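### Hypothermia and sessions under 60 min are removal criteria although temperature is the primary outcome; this conflicts with the intention-to-treat analysis and favours non-inferiority if lateral care is truly colder

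*Protocol article*

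**What the plan says.** - **Outcome (section 2.10).** The primary outcome is "Premature infant axillary temperature". Section 2.2 makes the trial a non-inferiority comparison, and section 2.5 sets the margin at 0.2 °C.
- **Removal (section 2.4, Study Population).** "Removal criteria: hypothermia or kangaroo care duration under 60" min. No temperature threshold is given there.
- **Withdrawal (section 2.15, Monitoring).** "Established withdrawal criteria are hypothermia or a Kangaroo care session less than 60 min". The same section has the main investigator check that each session was completed according to the protocol, and adds: "If that is not the case, the session will be discarded".
- **Bedside rule (section 2.8).** A reading below 36.5 °C leads to added cover and reassessment after 15 min. If still low, more cover is added, with a third assessment after another 15 min, "and kangaroo care will be suspended if the temperature remains" below 36.5 °C. Sessions are to last at least 60 min.
- **Analysis (section 2.13).** "Intention to treat (NNT) and protocol analyses will be performed". Deviations are examined if the two analyses conflict. Nothing says which set holds removed infants or discarded sessions.
- **Expected direction (Introduction).** The authors say that side-lying could challenge thermoregulation because less skin is in contact.

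**The concern.** A poor value on the primary outcome, arising after randomisation, is itself a ground for removal. An intention-to-treat analysis needs the infants and sessions that sections 2.4 and 2.15 set aside, so those sections and section 2.13 cannot all be applied as worded.

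The direction matters. A non-inferiority test has to protect against the new position being worse. If lateral care is colder, removal falls more heavily on the lateral arm and the remaining means move together, so a colder position can pass.

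Two features weaken the safeguards. Section 2.13 looks into deviations only when the two analyses disagree, and two sets that both lack the cold infants would tend to agree. Also, the research nurses know the allocation (section 2.7), and the main investigator, who checks the sessions, has unblinded access to data for the interim analysis (section 2.15).

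**Working it through.** **1. Inputs from the article (section 2.5).** 35 per arm, SD 0.16, margin 0.2 °C, α 0.05, power 80%, 10% loss. The stated sample size fixes the sidedness:

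n = 2(1.645 + 0.842)² × 0.16² / (0.3 − 0.2)² = 31.65, so 32 per arm; 31.65 / 0.9 = 35.2.

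This agrees with the stated 35 only for one-sided 0.05; one-sided 0.025 gives 46 after loss. (Planning on a 0.3 °C difference against a 0.2 °C margin is a separate question.)

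**2. Assumptions, not in the article.** Prone mean of 36.7, 36.8, 36.9 or 37.0 °C; normal temperatures; one analysed value per infant, although the trial records repeated sessions. Hypothermia is taken as below 36.5 °C, the lower limit of normothermia in the Introduction and the bedside threshold in section 2.8.

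**3. Shrinkage of the difference when one low reading removes the infant.** For an arm with mean μ and cut-off c, let a = (c − μ)/0.16. The share removed is Φ(a), and the mean of those kept is μ + 0.16 φ(a)/(1 − Φ(a)). With prone mean 36.8 and true deficit 0.2:

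- Prone: a = −1.875; 3% removed; mean of the rest 36.811.
- Lateral (μ = 36.6): a = −0.625; 27% removed; mean of the rest 36.672.
- Observed deficit: 36.811 − 36.672 = 0.14 instead of 0.20.

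For prone means 36.7/36.8/36.9/37.0 the observed deficit is 0.11/0.14/0.17/0.19. The lateral share removed is 50/27/11/3%, above the 10% loss allowance in three of the four cases.

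**4. False non-inferiority rate.** Simulation with the true deficit exactly at the margin; non-inferiority is claimed if the pooled-t one-sided 95% upper limit for prone minus lateral is below 0.2. In the three-reading rows the last reading is analysed, total SD stays 0.16, and added cover is given no effect; the within-infant correlation is assumed.

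| Rule for removal | 36.7 | 36.8 | 36.9 | 37.0 |
|---|---|---|---|---|
| Nobody removed | 5% | 5% | 5% | 5% |
| One reading < 36.5 °C | 83% | 52% | 20% | 8% |
| Three successive readings < 36.5 °C, correlation 0.8 | 56% | 23% | 9% | 6% |
| Three successive readings < 36.5 °C, correlation 0.5 | 32% | 12% | 6% | 5% |
| One reading < 36.0 °C | about 5% | about 5% | about 5% | about 5% |

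Repeat runs moved individual cells by up to about three percentage points. With no true difference between the arms, the one-reading rule leaves the estimate at about 0.00.

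**5. Do the two criteria overlap?** If the first low reading is at 15 min (t1 in Table 1), the second is at 30 min and the third at 45 min. Suspension at 45 min also makes the session shorter than 60 min. If the first low reading is at 30 min or later, suspension comes at 30 + 15 + 15 = 60 min or later, and the duration criterion need not be met.

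**The case against.** The strongest reply is that removal and withdrawal need not mean deletion. Section 2.13 plans an intention-to-treat analysis, section 2.8 has all sessions of the first five days monitored and recorded, and section 2.15 logs hypothermia as an adverse event. The criteria could be meant only to end participation and to define the per-protocol set. This stands in part: a reader might infer that thermal failures certainly vanish from every analysis, and the article does not say so. But it does say that sessions are discarded, and it places removal under the study population. The contradiction lies in the stated text; it is not a detail left to another document.

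Second, the largest figures rest on a rule that the article does not state. Section 2.4 gives no threshold, and section 2.8 suspends care only after three low readings. This stands: 83%, or the loss of half the lateral arm, is an upper-end result and not an estimate for this trial.

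Third, a reader might infer that the result is biased towards non-inferiority whatever the truth. It is not: the bias requires a colder lateral arm, which the Introduction raises only as a possibility. That is nevertheless the case the test exists to detect.

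Fourth, a session can be short because the parent chose its length, so short sessions are not all thermal failures, and the two criteria coincide only when cooling is early.

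**Conclusion.** The point holds as a conflict between outcome-dependent removal after randomisation (sections 2.4 and 2.15) and the intention-to-treat analysis (section 2.13). Under a truly colder lateral arm it pulls the observed deficit towards zero and raises the chance of a false non-inferiority claim.

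The size is conditional on three things the article does not give: the threshold for hypothermia, the number of low readings needed, and the arm means. At a true deficit of 0.2 °C the error rate, nominally 5%, ranges from no material change to about 83%. Under a three-reading rule at 36.5 °C it is about 5% to 56%. The effect is small when the prone mean is near 37.0 °C.

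Because it bears on the primary conclusion, it should be settled before analysis. The documents do not support saying that the data are certainly lost, that the bias is unconditional, or that any one of these rates applies.

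**What to change.** Confine the change to the analysis sets and the retention of data:

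1. State in sections 2.4, 2.13 and 2.15 that the two criteria do not remove infants or sessions from the intention-to-treat analysis, and reconcile the statement about discarded sessions with this.
2. Keep every randomised infant and every started session in that set, with all temperatures recorded up to and including the reading that triggered suspension.
3. Let the 60-min criterion define only the per-protocol set, without excluding sessions that ended because of low temperature.
4. Report by arm the number of infants with any reading below 36.5 °C, with added cover, or with suspension. Added cover can hide a colder arm, and the materials used are already collected (section 2.11).
5. State what hypothermia means in the removal and withdrawal criteria, since sections 2.4 and 2.15 give no threshold.

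The bedside suspension rule and the safety-withdrawal rule are left unchanged.

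The cost is wording and a little more analysis. The article does not assure data from sessions after a withdrawal, so the set would use what was recorded. The estimate may become less favourable to lateral care.
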